## Discussion

One of the most prevalent neurological complications associated with PHIV is PN. It has a negative impact on the disturbed lives of PHIV, a vulnerable and marginalized population. Safe, effective, and non-harmful non-pharmaceutical interventions are highly desirable to alleviate and treat PN symptoms in PHIV because there is no FDA-approved treatment for this condition. Surprisingly, research studies on non-pharmacological treatments for HIV-related PN are scarce. To the best of our knowledge, there are only seven non-pharmacological intervention studies on pharmacologic and non-pharmacologic treatments for HIV-related neuropathy pain, and the total number of participants in these seven studies is 742 (51). Our proposed trial will be, to the best of our knowledge, the first one to investigate the efficacy of TCM on HIV-related PN. Thus, it will make an important contribution to research and offer evidence on a possible, low-risk, noninvasive, non-pharmacological intervention to address HIV-related PN, an overlooked issue in PHIV. Researchers in a systematic review have found that there are very few serious adverse events related to massage therapies in general and massage related to pain (32). Thus, TCFM is a promisingly effective and safe intervention to treat HIV-related PN.

Based on traditional Chinese medicine, a person's health is achieved when his or her body's Qi (life force or vital energy) is balanced and unhindered. Blood flow is impeded when Qi is blocked, and pain may develop in the nearby area. The purpose of TCFM is to promote blood circulation and remove energetic blocks. As a result, Qi stagnation and related pain can be removed (25). Moreover, studies revealed that massage therapy could reduce inflammation and promote mitochondrial biogenesis that repairs damaged muscles (52).

This proposed trial has several major advantages. This trial offers a thorough, written research protocol that is transparent and reproducible. The methodology is written in detail and allows reproducibility. Moreover, several crucial HIV-related health outcomes are evaluated. Furthermore, the placebo massage is carefully designed with the intention of not activating acupuncture points or involving techniques of traditional Chinese massage. Thus, the results of this trial will add valuable evidence and implications to incorporating complementary medicine for HIV-related PN, a prevalent but overlooked issue in PHIV. To ensure consistency in the delivery of the intervention and placebo, the same two therapists will administer the TCFM and the placebo massage.

The main limitation of this proposed trial is that although blinded, participants will possibly realize the type of massage they have received. However, all massage-related studies are subject to this methodological flaw. A control group is still important to account for placebo effects (53). After the trial is completed, the therapists will instruct the participants on how to support their health and adopt lifestyle changes that will reenergize and clear pathogenic factors from the channel for long-term health benefits. Participants will be given instructions by the therapists on how to perform at home, convenient toe exercises, including kneading massage to the foot, specifically to the locations of GB 40 and 41, and rolling manipulation to the sole of the foot with a provided racquetball for pressure to KI 1.

In short, this proposed trial will provide important research evidence and clinical implications for the effectiveness of TCM in reducing HIV-related PN. We intend to share the research results at national and international academic conferences as well as regional HIV community events. We will also disseminate the results in peer-reviewed journals as open-access publications.

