**Outcomes:**

The primary outcomes, measured at baseline, end of TCFM/placebo, and twelve weeks after, include (1), lower extremity pain, (2) lower extremity functioning, and (3) health-related quality of life. The secondary outcomes, measured throughout the trial process, include (1) recruitment and completion rate (No. of referred, No. of eligible, No. of enrolled, No. of withdrawals, trial recruitment rate, and trial completion rate), (2) participants' safety (No. and severity of adverse events), (3) treatment adherence (average time of each message session, No. of completed sessions, and No. of missed sessions), and (4) compliance (No. of participants completing the trial following the initial group assignment).

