#### Step four: Expelling and clearing pathogenic factors

GB 40, Zulinqi (GB 41), and the sole of the foot will be massaged with major thenar kneading manipulations for three passes beginning with soft then more penetrating kneading movements from ankle GB 40, 41 to the plantar surface of the foot. Further treatment of the foot will include shaking manipulation and rotation to the ankle. To further generate Qi flow and clear pathogenic factors, toe rotation and pulling will be followed by rubbing of Shangqiu (SP 5) until the participant reports a warm sensation over the medial malleolus of the ankle.

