### The placebo massages

The same therapist will provide 6 weekly 25-min placebo massage sessions to participants in the placebo group. These sessions will include an assessment of the affected extremity's legs and toes for lesions and broken skin to avoid them during the massage. The provider will perform an open hand technique of gentle foot and toe rubbing without any point stimulation or other TCFM techniques.

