#### Primary outcome

PN-related pain, lower extremity functioning, and health-related quality of life will be collected at the first visit after consenting before randomization (baseline). This information will be collected again at their sixth visit after the TCFM/placebo massage (immediate impact) and 12 weeks after the competition of the trial (long-term effect).

1) The Short Form-McGill Pain Questionnaire-2 (SF-MPQ-2) will be used to measure PN-related pain (42). SFMPQ-2, consisting of 22 items from the McGill Pain Questionnaire (MPQ), can reflect both neuropathic and non-neuropathic pain. Each descriptor is ranked from 0 to 10 (0 indicates none; one indicates mild; ten indicates the worst pain possible). Total pain is the average of all 22 items, ranging from 0 to 10. The correlation of SFMPQ-2 with MPQ has been demonstrated.2) Lower extremity functioning will be measured by the Lower Extremity Functional Scale (LEFS) (score range 0–100) (43). A higher score indicates better lower extremity functioning. The LEFS has strong tes*t-*retest reliability, cross-sectional construct validity, and internal reliability (44). It was demonstrated that it could accurately identify changes in lower extremity musculoskeletal conditions in patients that are clinically significant (45).3) Health-related quality of life will be measured by the Medical Outcomes Study Questionnaire Short Form 36 Health Survey (SF-36) (score range 0–100) (46). A lower score indicates more disability, and a higher score indicates less disability. According to prior studies, the SF-36's reliability score was higher than 0.80 (46, 47).

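### Trial completion has two meanings in the protocol, so home self-massage teaching for both arms can fall before the 12-week primary comparison

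*Protocol article*

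**What the plan says.** **Timing of the teaching.** The Discussion states: "After the trial is completed, the therapists will instruct the participants on how to support their health and adopt lifestyle changes". It gives no visit or week.

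**Content and recipients.** The Discussion continues: "Participants will be given instructions by the therapists on how to perform at home, convenient toe exercises", and lists among them "kneading massage to the foot, specifically to the locations of GB 40 and 41, and rolling manipulation to the sole of the foot", with a racquetball supplied for pressure to KI 1. The sentence names participants in general and sets no restriction by arm.

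**Overlap with the active treatment.** Step four of TCFM reads: "GB 40, Zulinqi (GB 41), and the sole of the foot will be massaged with major thenar kneading manipulations". Step three rolls the sole from heel to toes and ends with pressing at KI 1. The placebo section defines the control as gentle rubbing "without any point stimulation or other TCFM techniques".

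**Timing of the last outcome visit.** The Primary outcome section puts it "12 weeks after the competition of the trial (long-term effect"), where the third word from the start of the time reference is evidently a misprint for completion. The abstract describes the same schedule as "measured at baseline, end of TCFM/placebo, and twelve weeks after".

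**Primary comparison.** The Statistical analysis section compares the arms in change from baseline at the last visit, for each primary outcome. The Sample size section sizes the trial on that contrast for the SF-MPQ-2 total.

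**A competing use of completion.** The Statistical analysis section defines the completion rate by completion at baseline and at follow-up visits.

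**The concern.** The teaching is timed by a term that the protocol uses in two incompatible ways. On one usage, staff could teach every participant TCFM manipulations at the start of the 12-week interval that ends in the primary comparison, and still be following the protocol.

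Two things would then be at stake:

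- **The question answered.** The last visit is meant to show the long-term effect of six TCFM sessions against six placebo sessions. With early teaching it would compare TCFM plus self-massage with placebo plus self-massage, and the placebo arm would have been handed techniques that the control was designed to leave out.
- **Blinding.** Placebo participants would be shown point techniques they had never received, while TCFM participants would recognise them. This could reveal allocation before the final pain and quality-of-life questionnaires. The protocol already concedes, under Blinding and in the Discussion, that participants may guess their arm.

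**Working it through.** **1. What completion means in each place**

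| Place in the protocol article | What it dates or counts | Meaning of completion it implies |
|---|---|---|
| Abstract, Outcomes | Last visit is twelve weeks after the end of TCFM/placebo | Does not use the term; fixes the visit relative to the sessions |
| Primary outcome | Last visit is 12 weeks after completion of the trial | End of the six sessions, if it is to agree with the abstract |
| Statistical analysis | Completion rate counts baseline and follow-up visits | End of follow-up |
| Discussion | Teaching follows completion of the trial | Not stated |

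The abstract and the Primary outcome section agree only if completion in the latter is the end of the sessions. Applied to the Discussion, that meaning allows the teaching any time from session six onward, so up to 12 weeks before the last visit. The meaning in the Statistical analysis section puts the teaching after the last visit.

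**2. Overlap of techniques**

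- Kneading at GB 40 and GB 41: TCFM step four.
- Rolling of the sole and pressure to KI 1: TCFM step three.
- Placebo: none of these.

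**3. The protocol's sample size, reproduced first**

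Inputs, all from the Sample size section: two-sided alpha 0.05, power 0.80, SD 2, difference 1, within-person correlation 0.8 (compound symmetric), 25% dropout at post-baseline visits, 1:1 allocation.

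With everyone seen at baseline and 75% seen at both later visits, the variance factor for the last visit is

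0.8² + (1 − 0.8²)/0.75 = 0.64 + 0.48 = 1.12.

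Then

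n per arm = 2 × 1.12 × (1.960 + 0.842)² × 2² / 1² = 70.33, rounded up to 71.

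This is the stated figure, so the sample size is not in question here.

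**4. What a smaller difference would do**

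The standard error of the last-visit difference with 71 per arm is 2 × √(2 × 1.12/71) = 0.355. Power = Φ(difference/0.355 − 1.960).

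Let g_P and g_T be the gains from self-massage in the placebo and TCFM arms. The last-visit difference becomes 1 − (g_P − g_T). It shrinks only if g_P exceeds g_T; with equal gains it stays at 1. The documents give neither quantity, so the rows below are assumed.

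| g_P − g_T (assumed) | Difference | Power with 71 per arm | n per arm for 80% power |
|---|---|---|---|
| 0 | 1.0 | 0.80 | 71 |
| 0.1 | 0.9 | 0.72 | 87 |
| 0.25 | 0.75 | 0.56 | 126 |
| 0.5 | 0.5 | 0.29 | 282 |

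**The case against.** The strongest reply is that the Discussion sentence means what it ordinarily says: the trial is over once the last assessment is done, and the teaching is a courtesy offered afterwards for long-term health. The completion rate in the Statistical analysis section supports this, since it counts follow-up visits. The early reading leans on one loosely worded, misprinted phrase, and where the abstract means the end of the sessions it says so directly. On the ordinary reading nothing is contaminated. This stands as far as it goes, and it rules out a claim that the teaching does come early.

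A reader might infer early teaching from the staffing: therapists deliver the six sessions and separate assessors are trained for data collection, so session six looks like the therapists' last contact. The protocol does not say that it is. The Discussion sentence itself provides for a further therapist contact, so that inference cannot date it.

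A reader might also infer that the between-arm difference must shrink. It need not. Both arms would be taught, and equal gains leave the difference unchanged. Dilution needs a larger gain in the placebo arm, for example because TCFM participants have less left to gain. That is plausible, but the documents do not support it with any figure.

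What the objection does not remove is the ambiguity. The Primary outcome section does use completion of the trial for the end of the sessions, and it is the section that dates the visit on which the primary comparison rests.

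**Conclusion.** The point holds as an unresolved inconsistency with a possible consequence for the primary contrast. It does not show that the placebo arm will receive active components before the endpoint: the text permits that and also permits the opposite.

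If the teaching came early, the change in what is being compared would follow directly from the content of the instruction and needs no numerical assumption beyond participants using what they are taught. The added threat to blinding is possible but cannot be sized. The loss of power is illustrative only: from 0.80 to about 0.72, 0.56 or 0.29 for assumed differences of 0.9, 0.75 or 0.5, each conditional on the placebo arm gaining more than the TCFM arm. The sixth-visit assessment would be unaffected provided the teaching followed it.

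The inconsistency should be corrected, because staff could follow the wording in the Primary outcome section in good faith and alter the last-visit comparison, and the remedy is small. Confidence is medium, since the intended timing may well have been after follow-up.

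**What to change.** Reconcile the abstract (Outcomes), Primary outcome, Statistical analysis and Discussion sections:

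1. Use one term for the end of the six sessions and a different one for the end of follow-up, and correct the misprint in the Primary outcome section.
2. State that, in both arms, the home-technique instruction and the ball are given only after that participant's 12-week outcomes have been recorded.

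The cost is a few words of protocol text. The downside is that the teaching may reach participants 12 weeks later than it otherwise would, and that it needs therapist contact at or after the last visit, or written instructions in its place. If teaching after follow-up was always intended, practice does not change.

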## Trial status

This trial was registered with ClinicalTrials.gov of the National Institute of Health on Oct 26, 2022 (ClinicalTrials.gov No: NCT05596123). The researchers expect to recruit participants starting in Feb. 2023 and ending in Feb 2025.

## Ethics statement

The University of Houston-Downtown Committee for the Protection of Human Subjects approved the proposed trial of this protocol after conducting an ethical review. Oral and written informed consent will be obtained from every participant.
